### Objectives {7}

Accordingly, the aim of this CAncer of Rectum REhabilitation Trial (CARRET) study is to evaluate the effectiveness of a pre- and post-surgical pelvic floor rehabilitation program on the bowel symptoms, pelvic floor function, and quality of life of rectal cancer patients up to 3 months after their rehabilitation. The secondary objectives are to assess adherence to home-based PFME and attendance to rehabilitation sessions and to perform intra and intergroup comparisons regarding bowel symptoms and anorectal function considering all time points (baseline, before stoma removal, immediately and 3 months and 1 year after pelvic floor rehabilitation).

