A booklet was designed for this study with these instructions, and exercises will be provided to the patients as well as an audio that will be sent to their cell phones using the WhatsApp application. The pelvic floor therapist will be given a mobile number with a WhatsApp account so they can send audios and contact patients to reinforce instructions for performing PFME at home. Patients will receive a WhatsApp message once a week to remind them about the exercises. A closer contact with the therapist may increase patients’ self-efficacy and adherence to the treatment [16]. In addition, patients will receive a diary to register the days when they exercise their pelvic floor in order to check adherence to home-based exercises.

Stage 2: Pelvic floor rehabilitation will be delivered in 4 sessions of pelvic floor physiotherapy 3–5 weeks before stoma removal, three times for week. Although anorectal function is not being required for fecal elimination in those with stoma, we will perform PFME and sensory and capacitive training to retrain this function and prevent leakage. In addition, patients will receive 5–8 sessions of pelvic floor physiotherapy starting approximately 2 weeks after stoma removal surgery, over a period of up to 1 month, three times per week, according to patients´ needs. Each session will last approximately 40 min.

Rehabilitation will start around 6–10 weeks after the surgery, depending on physician indication and stoma removal surgery.

The rehabilitation intervention will include pelvic floor exercises, electromyographic biofeedback, and capacitive and sensory training:

Pelvic floor muscle exercises (PFME) will be performed following the protocol of Bø and colleagues [17] who instructed participants to perform a daily total of 24 to 36 slow contractions (high-intensity maximal voluntary contraction with a 6 to 8 s hold). Each slow contraction will be followed by three-to-four fast contractions and then 6 s of rest. In addition, patients will be encouraged to contract the pelvic floor muscles before situations that increase intra-abdominal pressure, known as the “knack” [18]. Patients will be instructed to repeat these exercises at home every day after ostomy removal.

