### Outcomes {12}

Evaluations will take place at baseline (T1), around 3–5 weeks before stoma removal and before rehabilitation (T2), immediately after rehabilitation (T3), 3 months (T4), and 1 year after rehabilitation (T5).

The primary outcomes are the mean score of bowel symptoms and the mean score of anorectal function. The primary time point will be 3 months after finishing pelvic floor rehabilitation treatment.

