## Statistical methods

### Statistical methods for primary and secondary outcomes {20a}

Data will be maintained in printed questionnaires which will be registered on an Excel dataset. A monitor will check the completeness of data and rigorously control patient’s follow-up. Data will be analyzed with descriptive (mean, standard deviation, median, interquartile range, and frequencies) and inferential statistics at the program SPSS®. A normality test will be performed using Kolmogorov-Smirnov criteria. For variables which follow normality criteria, we will use an independent T test to compare groups. In the case of a non-normal distribution, we will use the Mann-Whitney U test. To compare variables between pre- and post-intervention, we will use a paired T test or a Wilcoxon test. A significance threshold of *p* < 0.05 will be adopted for all tests.

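### The secondary bowel-symptom comparisons include the stoma visit (T2) and within-arm paired tests with no defined starting visit, so they cannot show a treatment effect; the between-group comparison at T4 is not biased by this

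*Protocol article*

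**What the plan says.** The section on statistical methods for primary and secondary outcomes {20a} of the protocol article plans two kinds of test. Between arms: "For variables which follow normality criteria, we will use an independent T test to compare groups", with Mann-Whitney U if the distribution is not normal. Within arms: "To compare variables between pre- and post-intervention, we will use a paired T test or a Wilcoxon test". The same 0.05 threshold applies to all tests, so the paired tests are inferential. No visit is named as the *pre* or the *post* value.

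The Objectives {7} list as a secondary aim "intra and intergroup comparisons regarding bowel symptoms and anorectal function considering all time points", and the list of time points that follows includes the one before stoma removal. The Outcomes section {12} places T2 about 3 to 5 weeks before stoma removal and before the rehabilitation block. T3, T4 and T5 follow rehabilitation. On the primary analysis it says: "The primary time point will be 3 months after finishing pelvic floor rehabilitation treatment".

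The intervention description concedes, when explaining the sessions before stoma removal, that "anorectal function is not being required for fecal elimination in those with stoma". The Background says that LARS can improve over the first 2 years.

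**The concern.** There are two linked problems, both in the secondary analyses.

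**The T2 symptom scores.** The LARS score asks about incontinence for flatus and liquid stool, clustering and urgency. ICIQ-B covers bowel pattern and bowel control. In a patient whose stool leaves through a stoma, these items do not describe how the anorectum works. Comparing them at T2, within or between arms, says little about bowel function.

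**The paired tests.** A within-arm change contains everything that happens between the two visits. From T2 that includes stoma reversal, and from T1 it includes the resection. From either it includes natural recovery. The Background criticises earlier studies for lacking an unexposed comparison group, and a within-arm p-value sets aside the one that this trial has.

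At stake is what the secondary results can support. A significant paired change could be reported as benefit, or as deterioration after rehabilitation, when it shows only the passage of time and the reversal operation.

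**Working it through.** **1. What the trial is sized for.** Inputs from the Sample size section {14}: means 2.8 and 4.9 on ICIQ-B bowel control (difference 2.1), power 80%, alpha 0.05 (two-sided assumed), ratio 1/1. With SD 2.8 in both arms:

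n per arm = 2 × (1.960 + 0.842)² × 2.8² / 2.1² = 27.9, so 28 per arm and 56 in total.

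This reproduces the stated 56. The calculation is a two-group comparison of means, not a paired one.

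**2. What a paired change contains, by starting visit**

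| Start | State at start | What lies between start and T3 or T4, apart from treatment |
|---|---|---|
| T1 (baseline) | Before surgery | Resection, stoma period where there is one, reversal, recovery |
| T2 | Stoma in place; pre-surgical session already given in the experimental arm | Reversal, recovery |

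Neither start isolates the treatment. T2 is also not a true baseline, because the experimental arm has by then had its pre-surgical pelvic floor session. For the control arm, *pre- and post-intervention* has no literal meaning, since it receives no pelvic floor treatment in this period.

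**3. How often a paired test is significant with no treatment effect.** Assume that both arms shift by the same amount d, with n = 28 per arm. The protocol gives neither d nor the pre-post correlation r, so both are assumptions. The design difference of 2.1 points serves only as a yardstick for d.

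- SD of the change = SD × √(2(1 − r)). With SD 2.8 and r = 0.5 this is 2.8.
- Noncentrality = d × √28 / SD of the change. For d = 1 it is 1 × 5.29 / 2.8 = 1.89; for d = 2.1 it is 3.97.
- The rejection probability comes from the noncentral t distribution with 27 degrees of freedom, two-sided 0.05.

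| SD | r | d = 0 | d = 1 | d = 2.1 |
|---|---|---|---|---|
| 2.8 | 0 | 5% | 25% | 77% |
| 2.8 | 0.5 | 5% | 44% | 97% |
| 2.8 | 0.7 | 5% | 65% | nearly 100% |
| 4.49 | 0 | 5% | 13% | 39% |
| 4.49 | 0.5 | 5% | 21% | 67% |
| 4.49 | 0.7 | 5% | 31% | 87% |

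The SD of 4.49 is the root mean square of the two SDs in the Sample size section: √((2.8² + 5.7²)/2).

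**4. The between-arm test under the same shifts.** In 40,000 simulated trials (SD 2.8, r = 0.5, no treatment effect), the independent t test on the post values was significant in 4.9%, 4.8% and 4.9% of trials for shared shifts of 0, 2.1 and 4 points. It stays at its nominal level because the shift cancels between randomised arms.

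**The case against.** The strongest reply is that the analysis that answers the trial question is already there. A between-group test is planned, the primary time point is T4, the sample size is a two-group calculation, and the comparisons at all time points are a secondary aim. Reversal and natural recovery occur in both randomised arms and do not bias that contrast. This stands, and it limits the point to the secondary results.

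It can also be said that no passage makes T2 the *pre* value. That is right. A reader might infer it because T2 is described as the visit before rehabilitation, but T1 is labelled baseline and the intervention starts with a session before surgery. The choice may be settled in a fuller document. The objection does not rescue the paired tests, because step 2 shows that either start is confounded. Nor does it remove T2 from the bowel-symptom comparisons, which the Objectives include explicitly.

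A reader might further infer a 50% chance of a misleading pattern in which one arm is significant and the other is not. With the same rejection probability p in each arm, that chance is 2p(1 − p), which peaks at 50% when p = 0.5. It is about 49% at p = 44% but only about 6% at p = 97%, where both arms usually appear to change. The protocol does not say that efficacy will be judged by comparing within-arm p-values, so 50% is a maximum under an assumption and not an expected error rate.

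Finally, an unadjusted randomised comparison is valid, so adjusting for T1 is a gain in precision and not a correction of bias. How well a pre-surgical score predicts function after reversal is unknown.

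**Conclusion.** The point holds for the secondary analyses only. In patients with a stoma, ICIQ-B bowel pattern and control and LARS scores at T2 do not measure anorectal bowel function, yet the Objectives include that visit in the symptom comparisons. The paired tests have no defined start, and no available start separates treatment from reversal, surgery or recovery.

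With no treatment effect, 28 per arm, SD 2.8 and r = 0.5, a shared shift of 1 to 2.1 points gives a significant within-arm result in about 44% to 97% of trials. Over the assumed SDs and correlations, the range is 13% to 65% for 1 point and 39% to nearly 100% for 2.1 points. The size of the real shift is not in the document.

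The documents do not support the stronger conclusion that the trial's main result is confounded by stoma reversal: the between-group test at T4 keeps its error rate near 5% under the same conditions. Nor do they support a T2 artefact in every participant, since the concession about diversion is limited to those with a stoma.

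**What to change.** - **T2:** for patients with a stoma, do not use ICIQ-B bowel pattern or control, or the LARS score, as a baseline or comparison point. Manometry and general quality of life can stay at T2.
- **Within-arm change:** name the visits, report means and intervals descriptively, and drop the paired t and Wilcoxon p-values.
- **Effect claims:** base them on the between-group contrast at T4, with T3 and T5 secondary. Use ANCOVA or a repeated-measures model adjusted for the T1 value of the same measure in place of the unadjusted t test. If r is the correlation between T1 and the outcome, the residual variance falls by a factor of about 1 − r² (0.91 at r = 0.3, 0.75 at r = 0.5); at r = 0 almost nothing is lost. T2 should not be the covariate, because it follows the pre-surgical session.
- **T5:** say in the report that controls are invited to receive rehabilitation after the 3-month evaluation, so T5 is not a comparison with an untreated arm.

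The cost is a change of wording in the Objectives and statistical methods sections, and fewer questionnaire scores at one visit. No extra data or patients are needed, and the Trial status section says that recruitment had not started.

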### Interim analyses {21b}

Not applicable.

### Methods for additional analyses (e.g., subgroup analyses) {20b}

Subgroup analysis will be performed for gender groups.

### Methods in analysis to handle protocol non-adherence and any statistical methods to handle missing data {20c}

In cases of lost to follow-up rates lower than 20%, we will perform an intention-to-treat analysis, using single imputation procedures with the mean of the group to replace missing values.

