## Discussion

This paper presents a protocol for a prospective randomized controlled trial to study the effectiveness of pelvic floor pre(re)habilitation both prior to and after a low anterior resection for rectal cancer, versus no rehabilitation at all, on bowel symptoms, pelvic floor function, and quality of life. There is another similar study protocol published, but as it is a feasibility study, their primary outcome measure is the proportion of eligible patients approached who consented to and attended the educational session. The secondary outcomes included patient compliance, the acceptability of the intervention (assessed using qualitative interviews) and pelvic floor tone, patient bowel function, and quality of life [36]. Besides that, two systematic reviews showed promises of the benefits of PFME on bowel function after rectal cancer. However, the methodological limitations of the included studies justify the need of randomized controlled trials testing the effectiveness of pelvic floor rehabilitation to prevent LARS [11, 12].

This study is innovative because it will include prehabilitation, i.e., a session of pelvic floor physiotherapy prior to the surgery. A possible limitation of this study will be related to oncological results of the included patients, for example if the patient requires adjuvant chemotherapy and have other complications, will delay rehabilitation, which might affect the results. Furthermore, the long follow-up period added to by the social unrest in Chile that started in 2019 and COVID-19 outbreak in early 2020 might increase attrition rates or delay the study results.

The proposed research received ethics approval from Servicio de Salud Metropolitano Oriente [Orient Metropolitan Health Service], Santiago de Chile (approval date: October 08, 2019). Published results are expected in 2022.

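### Filling missing outcomes with the group mean and then running an ordinary test understates the standard error, and no analysis is fixed for loss of 20% or more

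*Protocol article*

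**What the plan says.** The protocol article treats missing data in one sentence, in the section on non-adherence and missing data {20c}. For loss to follow-up below 20%, "we will perform an intention-to-treat analysis, using single imputation procedures with the mean of the group to replace missing values". Nothing is stated for loss of 20% or more, and no adjustment of the variance is described.

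The section on statistical methods {20a} gives the tests. For normally distributed variables, "we will use an independent T test to compare groups". Otherwise, "In the case of a non-normal distribution, we will use the Mann-Whitney U test". A threshold of p < 0.05 "will be adopted for all tests". The primary time point is 3 months after rehabilitation (T4, Outcomes {12}).

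No attrition rate appears anywhere. Sample size {14} inflates only for exclusions due to anastomotic leakage. The Discussion names long follow-up, social unrest and the pandemic as factors that "might increase attrition rates or delay the study results".

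**The concern.** A patient whose missing score is replaced by the arm mean adds no information, yet the test treats that score as observed. Two things go wrong together. The filled values have no spread, so the standard deviation falls. They are also counted in the sample size, so the divisor rises. Both make the standard error too small, and they do so even in the most benign case, where data are missing completely at random.

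The primary comparison at T4 would then have intervals that are too narrow and a false-positive rate above the stated 5%. The intention-to-treat label also promises more than it delivers: under this rule the point estimate is simply the complete-case estimate, and whatever is known about the absent patient from earlier visits goes unused.

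Separately, making the analysis conditional on the loss rate leaves the plan without a stated analysis in the range where missing data threaten the comparison most.

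**Working it through.** **Inputs.** Sample size {14}: 31 per arm planned, 28 per arm before inflation. Statistical methods {20a}: t test or Mann-Whitney at 0.05. Section {20c}: mean-of-group filling, loss below 20%. Assumed here: the group is the randomised arm, losses are equal in both arms, and data are missing completely at random. For the exact results, data are also normal with equal variances.

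**The plan's own figure.** The sidedness of the tests is not stated. A two-sided 5% test with 80% power, difference 4.9 − 2.8 = 2.1 and SD 2.8 in both arms gives 28 per arm, or 56 in total, which matches the article. One-sided testing gives 44, so two-sided is used below. (The match needs the smaller of the two reported SDs in both arms. That is a separate matter.) Inflating for leakage, 56 × 1.109 = 62.1, in line with the stated 62, or 31 per arm.

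**Standard error.** Let n be randomised and k observed per arm, with observed SD s.
- Complete cases: SE of an arm mean = s/√k.
- After filling: the mean is unchanged, the variance becomes s²(k−1)/(n−1), and the SE becomes s√[(k−1)/(n(n−1))].
- Ratio of filled to complete-case SE = √[k(k−1)/(n(n−1))], roughly k/n.

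**Type I error.** The test rejects when the complete-case t statistic, on 2k−2 degrees of freedom, exceeds the critical value on 2n−2 degrees of freedom multiplied by that ratio. For n = 31 the critical value is 2.000 (60 df).

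| n per arm | Missing per arm | SE ratio | True type I error | Coverage of 95% interval |
|---|---|---|---|---|
| 31 | 1 (3.2%) | √(870/930) = 0.967 | 5.8% | 94.2% |
| 31 | 2 (6.5%) | √(812/930) = 0.934 | 6.7% | 93.3% |
| 31 | 3 (9.7%) | √(756/930) = 0.902 | 7.7% | 92.3% |
| 31 | 5 (16.1%) | √(650/930) = 0.836 | 10.1% | 89.9% |
| 31 | 6 (19.4%) | √(600/930) = 0.803 | 11.5% | 88.5% |
| 28 | 5 (17.9%) | √(506/756) = 0.818 | 10.8% | 89.2% |

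Six of 31 is the ceiling, since 7/31 = 22.6% passes 20%.

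**Simulation, 31 per arm, 6 missing per arm, 10,000 trials per scenario.**
- t test after filling: 11.6% with normal data, 12.2% with SDs of 2.8 and 5.7, 11.2% with exponential data.
- Mann-Whitney after filling: 15.9% with normal data, 14.3% with exponential data. The rank test suffers more because each arm's filled values are tied at that arm's own mean, so every filled-against-filled comparison points the same way.
- Observed normal data only, nothing filled: 5.1% (t test) and 4.8% (Mann-Whitney).

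**The case against.** **A separate analysis plan may exist, and an article condenses.** That would excuse a missing detail. It does not excuse a method that the article states and that gives wrong error bars.

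**A reader might infer that intention-to-treat is abandoned at 20% loss.** The article does not say so. It states what happens below 20% and is silent above, and a fuller document might fill that gap. What stands is narrower: intention-to-treat is promised only below 20%, and no analysis is given beyond it.

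**A reader might also infer that the authors expect high attrition.** The Discussion says only that attrition might increase, as a possible limitation, and gives no rate. The 11.5% figure therefore belongs to the protocol's own ceiling and is not a forecast. With 1 or 2 missing per arm the inflation is small (5.8% and 6.7%).

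**The group could mean both arms pooled.** Simulated type I error for the t test then stays near 5% (5.2% with 6 missing per arm), but the estimated effect is pulled toward zero. The arm is the more natural reading, because the article uses the word for the control and experimental groups. The pooled reading would be a different defect and not a defence.

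**Data may not be missing at random.** Bias could then go in either direction, and the calculation above does not address it. The understated standard error would remain.

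**Conclusion.** The point holds. Filling with the arm mean and then applying an ordinary test gives the complete-case estimate with a standard error that is too small. At the protocol's own limit the standard error is about 20% too small and the nominal 5% error becomes about 11.5% for the t test and 14% to 16% for Mann-Whitney. At low loss it is close to nominal. Where in that range the trial falls depends on a loss rate that the documents do not give.

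This rests on reading the group as the randomised arm, on data missing completely at random, on equal loss in the two arms and on two-sided testing. As planned, the imputation is worse than leaving the gaps unfilled: the estimate is the same and the error rate is higher. On the 20% condition, the finding is only that the plan fixes no analysis at or above that level.

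**What to change.** Delete the mean imputation and the 20% condition. State that patients are analysed in their allocated arm whatever the loss, with a method that carries the missing-data uncertainty. Two suitable choices are:
- A likelihood-based repeated-measures model on T3 and T4 with the T1 score as covariate, reading the contrast at T4. Leave T5 out of this model: controls are offered rehabilitation after the 3-month evaluation (Intervention description {11a}, Provisions for post-trial care {30}), so their later scores should not inform missing T4 values.
- Multiple imputation by arm from earlier scores. T2 is taken before stoma removal, so its value for predicting bowel symptoms at T4 should be considered before it is used.

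At minimum, analyse the observed data without filling in means. In the simulations this restored an error rate of about 5%.

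Also state how the analysis set fits with the planned exclusion of patients with clinically relevant anastomotic leakage (Eligibility criteria {10}, Sample size {14}), because that exclusion and an analysis of everyone randomised cannot both stand unqualified.

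The cost is a few sentences of text and routine procedures in standard software. Intervals will be wider than under the current rule, by about a quarter at the ceiling (1/0.803 = 1.25) if only observed data are used, and that width is the honest one.

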### Plans to give access to the full protocol, participant level-data, and statistical code {31c}

In case of audits of health authorities and funder or other researchers needing to access data for scientific purposes, we will give access to the full protocol, participant level-data, and statistical code.

